#### Secondary endpoints

Repeat ipsilateral pleural intervention including diagnostic aspiration, e.g., for the investigation of possible infection will be identified as aboveTime to symptomatic effusion recurrence will be measured from the date of procedure, by performing radiological investigations if the participant describes worsening dyspnoea at a study visit. Recurrent effusion is defined as greater than 25% increase in opacification on chest x-ray (CXR) on the side of the intervention, and evidence of pleural fluid on ultrasoundAll-cause and pleural-related hospital days will be measured. Length of stay post-procedure and hospitalisation for any cause (except for elective admissions for chemotherapy) will be recorded for all participants post-enrolment until the end of follow-up period or death. Admissions will be analysed as total admission days (and number of episodes) and as pleural-related admission daysDegree of breathlessness will be measured using a 100-mm visual analogue scale (VAS), which is a validated score of dyspnoea in MPE [23]. The VAS is a 100 mm line anchored with “no breathlessness” at 0 mm and “worst breathlessness imaginable” at 100 mm and will be done during the aforementioned outpatient reviews. Two independent researchers will measure all VAS scores and the mean score will be calculated. Differences in scores of more than 3 mm in both measurements will be repeated by the same observersPain will be assessed using a 100-mm VAS with timing and measurement as for breathlessnessQuality of Life (QoL) will be measured using two instruments, the EQ-5D-5L questionnaire and VAS QoL, both employed as primary or secondary end-points in previous RCTs [23, 40]. VAS QoL records self-rated quality of life on a 100 mm line, anchored with “best imaginable quality of life” at one end-point and “worst imaginable quality of life” at the other. QoL will be measured at each study visitPhysical activity patterns will be evaluated by a well-validated triaxial accelerometer (ActiGraph GT3X+, Pensacola, FL, USA) providing an indication of functional status [41]. Standard data processing will be applied and the weekly duration of low, moderate, and vigorous-intensity physical activity determined in accordance with established ranges. This will be performed at the lead-site onlyAdverse events will be recorded from time of enrolment until end of follow-up or death. An adverse event is defined as any complication associated with the IPC or VATS pleurodesis, including, but not limited to, pleural infection, cellulitis, pain, symptomatic loculation +/− requirement of intrapleural fibrinolytics, tube blockage, catheter tract metastases, parenchymal air leak, etc., and any peri/post-procedural complications such as prolonged air-leak, atelectasis, pneumonia, cardiovascular complications, acute kidney injury, or drop in haemoglobin requiring transfusionEconomic analysis will be performed by obtaining inpatient costs from the hospital. Outpatient pleural care costs and equipment utilisation will be noted (Western Australia only)Overall survival will be recorded from date of enrolment to death or end of study follow-up

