### Standard care and follow-up

Participants in both arms will be managed by their own clinical teams and receive all other usual medical treatment (including chemotherapy and radiotherapy). All participants and carers will have access to the research team should any concerns arise. This cohort will remain under the continued care of a physician or thoracic surgeon following trial completion.

Participants are advised prior to enrolment that they are free to withdraw from the trial at any time if they so wish. Following randomisation, changes to the intervention plan may be made at the discretion of the treating physician or due to participant request.

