### Outcomes

Data will be collected by the site investigators from the participant at follow-up visits (see 16) and from their hospital record.

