#### Primary endpoint

The primary outcome is the need for an ipsilateral pleural intervention within 12 months of randomisation for symptomatic recurrence of pleural effusion. Pleural intervention will be defined as an ipsilateral surgical procedure, chest drain insertion or thoracentesis with therapeutic intent.

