
### Participant timeline

Baseline data will be collected once informed consent has been obtained. Data collected will include demographics, ASA, ECOG performance status, questionnaires (VAS breathlessness, VAS QoL, VAS pain, EQ-5D-5L), comorbidities, malignancy type, stage and treatment, baseline bloods (full blood picture, albumin, lactate dehydrogenase, C-reactive protein), baseline CXR findings, baseline ultrasound thorax and pleural effusion data including laboratory results and previous interventions.

The assigned intervention will be scheduled to occur within 2 weeks of randomisation. Participants will be followed up between day 7 and 10 post-procedure, monthly to 6 months, at 9 months, and at 12 months or death if sooner (Table 1, Fig. 1). There will be a visit ‘window’ initially of ±3 days surrounding the early visits. Later visit dates will have a larger visit window.

**Table 1 Tab1:** Schedule of treatment for each visit and follow-up procedures

	Study period								
	Pre-procedure		Post-procedure						
	Enrolment	Within 2/52	Days post-procedure				Months		
Timepoint	***T-1***	***T0***	***D1***	***Discharge***	***D7-10***	***D28***	***2–6***	***9***	***12***

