**Assessments:**									
***Questionnaires (VAS QoL, dyspnoea, pain; EQ5D5L)***	X				X				X
***Logbook commencement***			X						
***Logbook collection***						X			
***Procedure-related data collection***				X					
***ActiGraph to participant—lead site only***			X			X	X		
***Assessment for pleurodesis***^**d**^					X	X	X	X	X
***Assessment for re-intervention***			X		X	X	X	X	X
***Adverse event review***			X		X	X	X	X	X

^a^Bedside ultrasound mandatory at baseline only

^b^Blood tests to include FBC, albumin, LDH, and CRP

^c^CXR mandatory at baseline, days 7–10, and months 1, 3, 6, 9, and 12

^d^IPC arm only. Spontaneous pleurodesis is defined as < 50 ml drain output on 3 consecutive drainages at least 24 h apart

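### Time to symptomatic recurrence is tied to dyspnoea described at a study visit, so an effusion drained between visits can be a primary event yet be missed, or dated late, as a recurrence

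*Protocol article*

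**What the plan says.** All references are to the protocol article.

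- **Secondary endpoints.** Time to symptomatic recurrence runs from the date of the procedure and is measured "by performing radiological investigations if the participant describes worsening dyspnoea at a study visit". The definition has two parts: "Recurrent effusion is defined as greater than 25% increase in opacification on chest x-ray (CXR) on the side of the intervention", together with pleural fluid seen on ultrasound.
- **Participant timeline.** After a visit at days 7 to 10, follow-up is "monthly to 6 months, at 9 months, and at 12 months or death if sooner". Early visits have a window of 3 days either side; for the rest, "Later visit dates will have a larger visit window".
- **Primary endpoint.** The primary outcome is the "need for an ipsilateral pleural intervention within 12 months of randomisation for symptomatic recurrence of pleural effusion". A qualifying intervention is a surgical procedure, a chest drain or a therapeutic thoracentesis on the same side. It need not be linked to a study visit.
- **Outcomes (introduction).** Data are collected "at follow-up visits (see 16) and from their hospital record".
- **Standard care and follow-up.** "All participants and carers will have access to the research team should any concerns arise".
- **Table 1, footnotes.** "CXR mandatory at baseline, days 7–10, and months 1, 3, 6, 9, and 12". Ultrasound is compulsory at baseline only.

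**The concern.** A time-to-event endpoint needs a rule for what counts as an event and when it happened. The article gives a trigger for imaging, and the trigger is a symptom described at a visit. A participant who becomes breathless between visits, is drained and feels well again may have no worsening dyspnoea to describe at the next visit. Drainage may also have removed the chest x-ray and ultrasound findings that the definition requires. That participant has a primary event, by definition for symptomatic recurrence, but need not have a recurrence on the secondary endpoint. The trial could then report more re-interventions for symptomatic recurrence than symptomatic recurrences. Where the recurrence is still present at the next visit, it may be dated there rather than when it arose.

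The arms also differ in how fluid is relieved between visits. After VATS it takes a new procedure. With an indwelling catheter, drainage at home may be enough. A visit-based trigger may therefore work differently in the two arms of an open-label trial.

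**Working it through.** **Plan's own figure.** The article gives no figure for the recurrence endpoint. Its sample size is used here only for expected event counts, and it reproduces. For 5% v 25%, two-sided 5% level (sidedness assumed) and 90% power, the uncorrected formula is [1.960 × √(2 × 0.15 × 0.85) + 1.282 × √(0.05 × 0.95 + 0.25 × 0.75)]² / 0.20² = 64.9, so 65 per group. The continuity correction gives 75. Adding 4 per group gives 79, or 158 in total.

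**Step 1: one case under both rules.** Take a participant drained by therapeutic thoracentesis for a symptomatic effusion in month 7 and comfortable at month 9.

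- *Primary endpoint:* an event, because a listed intervention was done for symptomatic recurrence within 12 months.
- *Time to recurrence:* the trigger is not met at month 9. The compulsory month-9 chest x-ray may no longer show the required increase, and ultrasound is not compulsory then.

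The compulsory x-rays do not shorten the gaps, because all those after baseline coincide with visits.

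**Step 2: gaps between visits.** Visit days after the procedure, taking the middle of days 7 to 10, are 8.5, 28, 61, 91, 122, 152, 183, 274 and 365. The gaps are 8.5, 19.5, 33, 30, 31, 30, 31, 91 and 91 days. The longest possible delay is thus about one month up to month 6 and about three months (91 days) after it. The wider late windows could add a little.

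**Step 3: mean delay if a recurrence is dated at the next visit.** Delay = next visit day − true recurrence day.

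*Uniform timing over 365 days* has a closed form: sum of squared gaps / (2 × 365) = 21,825.5 / 730 = 29.9 days.

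*Early clustering* is represented by an exponential distribution truncated at 365 days, F(t) = (1 − e^(−λt)) / (1 − e^(−365λ)), with λ set so that F(median) = 0.5. Each timing was simulated with 400,000 draws.

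| Assumed timing | Mean delay (days) | After month 6 | Delayed more than 31 days |
|---|---|---|---|
| Median 30 days | 14 | 1.4% | 3.6% |
| Median 60 days | 18 | 11% | 10% |
| Median 90 days | 22 | 22% | 17% |
| Uniform over the year | 30 | 50% | 33% |

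The 30-day median is the only timing figure in the article. The Introduction gives it for re-intervention after VATS in a retrospective review of mesothelioma. The other timings are assumptions that show the range.

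**Step 4: where the events lie.** At the design rates, 0.25 × 75 = 18.75 (about 19) VATS and 0.05 × 75 = 3.75 (about 4) IPC participants need re-intervention. If recurrence follows re-intervention, 0.25 / 0.30 = 83% of events are in the VATS arm. This is a share of events. It does not measure how well events are captured in each arm.

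**The case against.** The strongest reply is that this is a drafting gap in a condensed article. The text does not say that recurrence is found only at visits, nor that the visit must be a scheduled one. The hospital record is named as a source for all outcomes, participants can contact the team at any time, and unscheduled visits are mentioned (for missed visits, under the strategies for adherence and retention). No event date is stated, and operational dating is often left to the full protocol or SAP. Recurrence on imaging and re-intervention are also different constructs and need not coincide.

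Much of this stands. Recurrences drained in hospital can be found, and dating at the visit is an inference. But the article does state how this endpoint is to be measured, and none of the other sections says that an effusion found elsewhere counts as a recurrence, or on which date. The constructs are also linked by the article itself, because the primary outcome counts interventions done for symptomatic recurrence.

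A reader might go further and infer that the rule under-counts recurrence mainly in the VATS arm. The documents do not support that. The same rule applies to both arms, and home drainage through a catheter can relieve symptoms and remove fluid before a visit, masking recurrence in the IPC arm. The 83% share in the working shows where events are expected, not where they are lost.

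**Conclusion.** The point holds for one secondary endpoint. The stated trigger allows a between-visit recurrence to be a primary event and yet be missed on the recurrence endpoint. It may also delay dating by at most about one month before month 6 and about three months after it. The mean delay is about 14 to 30 days, given the assumed timing distributions and dating at the next visit. If recurrences cluster as early as the 30-day median suggests, late dating is modest and only about 1% fall in the three-month gaps. The missed events and the mismatch with the primary endpoint remain.

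How many recurrences would be missed cannot be derived from the article. One could assume that 25% or 50% are drained before the next visit and never captured, and so turn a 25% recurrence rate into roughly 18% or 12%. Those shares have no source in the document, they ignore hospital-record capture, and 25% is a re-intervention rate.

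Ascertainment may differ by arm, in a direction that is not established. The primary outcome, including its competing-risks analysis, is defined by the intervention and does not depend on this trigger.

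**What to change.** Amend the endpoint definition in the protocol or SAP before the data are analysed:

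1. Count a recurrence identified at any contact, scheduled or not, or in the hospital record.
2. Date it at the earliest of (a) imaging that meets the existing chest x-ray and ultrasound definition, or (b) an ipsilateral pleural intervention, as listed for the primary endpoint, done for symptomatic effusion.
3. Apply the rule identically in both arms, and state how fluid drained through an IPC already in place is treated for this endpoint.
4. Report a sensitivity analysis limited to imaging-confirmed recurrences.

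The cost is a few sentences and one extra analysis. The hospital record is already a data source, and re-intervention is already assessed at follow-up (Table 1). The drawbacks are that unscheduled imaging is less standardised and that events dated by an intervention may lack x-ray and ultrasound confirmation; the sensitivity analysis addresses this. The sample size does not change.

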
### Participant timeline

Baseline data will be collected once informed consent has been obtained. Data collected will include demographics, ASA, ECOG performance status, questionnaires (VAS breathlessness, VAS QoL, VAS pain, EQ-5D-5L), comorbidities, malignancy type, stage and treatment, baseline bloods (full blood picture, albumin, lactate dehydrogenase, C-reactive protein), baseline CXR findings, baseline ultrasound thorax and pleural effusion data including laboratory results and previous interventions.

The assigned intervention will be scheduled to occur within 2 weeks of randomisation. Participants will be followed up between day 7 and 10 post-procedure, monthly to 6 months, at 9 months, and at 12 months or death if sooner (Table 1, Fig. 1). There will be a visit ‘window’ initially of ±3 days surrounding the early visits. Later visit dates will have a larger visit window.

**Table 1 Tab1:** Schedule of treatment for each visit and follow-up procedures

	Study period								
	Pre-procedure		Post-procedure						
	Enrolment	Within 2/52	Days post-procedure				Months		
Timepoint	***T-1***	***T0***	***D1***	***Discharge***	***D7-10***	***D28***	***2–6***	***9***	***12***
**Enrolment:**									
**Clinical assessment**	X	X	X		X	X	X	X	X
**Bedside ultrasound**^**a**^	X				X	X	X	X	X
**Informed consent**	X								
***Baseline data collection***	X								
***Blood tests***^**b**^	X								
***CXR***^**c**^	X				X	X	X	X	X
**Randomisation (IVRS)**	X								
**Interventions:**									
***Drainage procedure (VATS or IPC)***		X							
**Assessments:**									
***Questionnaires (VAS QoL, dyspnoea, pain; EQ5D5L)***	X				X				X
***Logbook commencement***			X						
***Logbook collection***						X			
***Procedure-related data collection***				X					
***ActiGraph to participant—lead site only***			X			X	X		
***Assessment for pleurodesis***^**d**^					X	X	X	X	X
***Assessment for re-intervention***			X		X	X	X	X	X
***Adverse event review***			X		X	X	X	X	X

^a^Bedside ultrasound mandatory at baseline only

^b^Blood tests to include FBC, albumin, LDH, and CRP

^c^CXR mandatory at baseline, days 7–10, and months 1, 3, 6, 9, and 12

^d^IPC arm only. Spontaneous pleurodesis is defined as < 50 ml drain output on 3 consecutive drainages at least 24 h apart

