### Statistical plan

Data will be analysed on an intention-to-treat basis and per protocol basis. The primary outcome will be analysed using a Fisher’s exact test for comparing two proportions and subsequent logistic regression analyses allowing adjustments for minimisation variables. A secondary analysis of the primary outcome will use a competing risks time to event analysis with the competing risk of death. For the secondary outcomes, e.g., hospital days and VAS measurements, the difference between the groups will initially be examined using two sample *t*-tests and further adjustments will be made for minimisation variables. Subsequent analyses will consider the repeated VAS scores measured on the same patient and missing VAS scores (assuming that missing scores are missing at random) and will include a time by treatment interaction term along with random intercepts and time effects as appropriate. An interim analysis is planned after the recruitment and follow-up of 60–80 participants.

The research team will document as accurately as possible the reasons for any non-completion or missing data, thereby minimising truly absent data. The expected dropout rate from patient death has been factored into the power calculation and is based on survival figures and previous studies.

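### Table 1 marks the questionnaires at two follow-up visits where the text calls for nine; the two cannot both be followed, and the planned repeated-measures VAS analysis needs the fuller schedule (secondary outcomes only)

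*Protocol article*

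**What the plan says.** All references are to the protocol article.

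- **Secondary endpoints.** Quality of life (EQ-5D-5L and VAS QoL) is to be taken at every study visit. The breathlessness VAS "will be done during the aforementioned outpatient reviews", and the pain VAS follows the same timing.
- **Participant timeline, text.** After a visit at day 7–10, follow-up is "monthly to 6 months, at 9 months, and at 12 months or death if sooner". Baseline data include the "questionnaires (VAS breathlessness, VAS QoL, VAS pain, EQ-5D-5L" set, so text and table agree at enrolment.
- **Table 1, Assessments.** One row, "Questionnaires (VAS QoL, dyspnoea, pain; EQ5D5L", covers all four instruments. It is marked at enrolment, D7-10 and month 12. The cells for D28, months 2–6 and month 9 are empty, and no footnote explains this.
- **Statistical plan.** "Subsequent analyses will consider the repeated VAS scores measured on the same patient"; the model "will include a time by treatment interaction term along with random intercepts and time effects as appropriate".

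**The concern.** The text and the table give different collection schedules for the same four instruments. If some sites follow the text and others the table, whether a score exists between day 10 and month 12 will depend on site practice.

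Breathlessness, pain and quality of life are the outcomes that patients report themselves. Under the table's schedule they would be seen once early and once at the end. The early point, day 7–10, falls close to the hospital stay that the Introduction quotes for VATS pleurodesis (5.8 to 10.3 days). The Introduction also names intercostal neuralgia as a common long-term complication after VATS, yet pain would go unmeasured by questionnaire from day 10 to month 12. A participant who dies before month 12 would contribute a baseline score and one early score. A score that was not collected cannot be recovered later, and recruitment began in April 2019 (Trial status).

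**Working it through.** The plan states no figure on this point, so there is none to reproduce. The check sets the two schedules side by side, then illustrates the effect on precision.

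**1. Count the visits**

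| Source | Post-procedure questionnaire points | Number |
|---|---|---|
| Text (Secondary endpoints with Participant timeline) | day 7–10; months 1, 2, 3, 4, 5, 6; month 9; month 12 | 1 + 6 + 1 + 1 = 9 |
| Table 1 | D7-10; month 12 | 2 |

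The difference is 9 − 2 = 7 assessments: months 1 to 6 and month 9. The gap between the table's two points is 365 − 10 = 355 to 365 − 7 = 358 days.

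**2. Is the row complete as printed?** Table 1 has nine timepoint columns and the questionnaire row has nine cells. The rows for clinical assessment, chest x-ray, re-intervention and adverse events carry separate marks at D28, months 2–6 and month 9. Where the table qualifies a mark, as for ultrasound and chest x-ray, it uses a footnote.

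**3. What the model needs.** With two follow-up points, a time-by-treatment term can compare only the change from day 7–10 to month 12; the course between them is not observed. If baseline enters as a covariate, a random intercept, a random slope, their covariance and a residual variance make four parameters. The covariance matrix of two visits has three distinct elements, so that model is not identifiable. With baseline as a response there are three time points and it can be fitted, but on little information.

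**4. Illustration of precision.** The article gives no correlation between visits. Assume equal correlation r between all visits, unit variance, complete data, and the mean of k follow-up scores as the quantity of interest.

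- Without baseline adjustment: variance = (1 + (k − 1)r)/k.
- With baseline adjustment: variance = (1 + (k − 1)r)/k − r².
- The standard-error ratio is the square root of the variance for k = 2 over that for k = 9.

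| r | Unadjusted, k = 2 / k = 9 | SE wider by | Adjusted, k = 2 / k = 9 | SE wider by |
|---|---|---|---|---|
| 0.4 | 0.700 / 0.467 = 1.50 | 22% | 0.540 / 0.307 = 1.76 | 33% |
| 0.5 | 0.750 / 0.556 = 1.35 | 16% | 0.500 / 0.306 = 1.64 | 28% |
| 0.7 | 0.850 / 0.733 = 1.16 | 8% | 0.360 / 0.243 = 1.48 | 22% |

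The Statistical plan names adjustment for the minimisation variables and does not mention baseline score, so both columns are shown.

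**The case against.** The best defence is that the intent is clear. Secondary endpoints and the Statistical plan both presuppose repeated scores, and a single table row disagrees, so this may be a slip in an article that condenses a fuller protocol. Case report forms and operating procedures exist separately (Data Availability), and nothing shows that sites work from this table. That stands, and it limits what can be said about the data actually collected. It does not reconcile the two statements in print.

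A schedule table can also mark the two ends of a range and join them with a line, which would bring the row into agreement with the text. This cannot be wholly excluded, but it is unlikely here, because the neighbouring rows are marked cell by cell across the same columns.

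The visit-by-visit rule is explicit only for quality of life. For breathlessness and pain it rests on reading the outpatient reviews as the follow-up visits, which is the natural reading.

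Four stronger readings are tempting, and the article does not support them:

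- **That no patient-reported data at all would be collected for almost a year.** Table 1 also lists "Logbook commencement" at D1, with collection at D28. The logbook's content is not described, so it may hold some patient-recorded data in the first month.
- **That month 12 would be reached by few, judging by the Introduction's survival figures.** Those medians (as short as 4 months in lung carcinoma, 12 months in mesothelioma) describe malignant effusion generally. This trial selects for predicted survival above 6 months and good performance status. Some deaths before month 12 are to be expected, but these figures do not size them.
- **That 28% is the loss of precision.** It needs a baseline adjustment that the Statistical plan does not state; without it the figure at r = 0.5 is about 16%.
- **That the trial's main result is at risk.** The primary endpoint is re-intervention, and neither its analysis nor the sample size uses these questionnaires.

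**Conclusion.** The contradiction is real and lies within the current text: nine post-procedure assessments by the text against two by Table 1. It is more than clerical, because following the table would remove seven of the nine points on which the repeated VAS analysis relies and leave its time-by-treatment term on two. For the mean follow-up score, standard errors would be roughly 8% to 33% wider over correlations of 0.4 to 0.7, depending on baseline adjustment. That range rests on assumed correlations, complete follow-up and an average-score estimand, none of which the article specifies. The point concerns secondary outcomes only. The article does not show which schedule sites have used.

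**What to change.** Mark the questionnaire row of Table 1 at D28, months 2–6 and month 9, so that it agrees with Secondary endpoints and with the repeated-measures analysis in the Statistical plan. State that this schedule applies to the breathlessness, pain and QoL VAS and to EQ-5D-5L, and confirm it to all sites. This direction is the better supported one, since both of those sections presuppose repeated scores. The cost is a table correction, a note to sites, and a few minutes of short questionnaires at visits that participants already attend.
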